#### 2.7.1 Selection of implementation strategies

Assessing barriers and facilitators to implementation was used in selecting the implementation strategies. A pragmatic approach was used building on previous experience and dialogue with MCH and ECEC staff, considering and balancing feasibility, impact, and cost. Moreover, all implementation strategies are in line with those deemed feasible and important by the ERIC-framework (Expert Recommendations for Implementing Change) (57) and adjusted to context (57) (**Tables 3**–**5**). The implementation strategies and their operationalization and justification are presented in **Tables 3**–**5**. The strategies are grouped according to the nine categories or clusters developed through a stakeholder participatory approach in the ERIC-study (55).

#### 2.7.2 Implementation strategies targeting organizational level

We will employ a set of seven implementation strategies to target the political and administrative leadership level in the municipality, including assessing barriers and facilitators to implementation, local consensus discussions and coalition building. Close collaboration with the municipal public health coordinator is considered essential for implementation. A co-creation process with stakeholders in the municipality including politicians resulted in a systems-map reflecting what they as a group consider the main determinants of child diet. A pre-existing formal agreement between the University and the intervention municipality facilitated access to the different settings (**Table 3**).

#### 2.7.3 Implementation strategies targeting parents and MCH staff (individual level)

We have used three strategies targeting pregnant women and parents directly, all of which relate to tailoring and promoting adaptability of the Nutrition Now resource (**Table 4**). All texts and videos are provided in English and Arabic in addition to Norwegian to reach culturally diverse groups. Regular reminders with emails linking to age specific topic will be sent to the parents to promote use of the Nutrition Now resource.

We also employ a set of implementation strategies targeting MCH staff (**Table 4**) within the categories “use evaluative and iterative strategies”, “adapt and tailor to context”, “develop stakeholder interrelationships”, “train and educate stakeholder” and “support clinicians”.

#### 2.7.4 Implementation strategies targeting ECEC staff

We will utilize a set of implementation strategies targeting ECECs (**Table 5**). These include the categories “use evaluative and iterative strategies”, “provide interactive assistance”, “adapt and tailor to context”, “develop stakeholder interrelationships”, “train and educate stakeholder”, “support clinicians”, “engage consumers” and “change infrastructure”. Identifying team leaders at each ECEC unit is regarded as a crucial strategy as they are important implementation champions to oversee that implementation takes place. They will also participate in short iterative interviews to closely monitor the implementation process.

### 2.8 Data collection

Quantitative and qualitative data will be collected in the different parts of this study (**Figure 2** and **Table 1**).

*Quantitative data* for the effectiveness evaluation will be generated from questionnaires and objective measures. Questionnaire data will be obtained from i) pregnant women and parents of 0-2-years-olds, assessed during pregnancy, at child ages 6 weeks, 6 months, 12 months, 18 months, 24 months and ii) ECEC staff, assessed at baseline (pretest) and after 7 months (posttest).

**Figure 4** provides an overview of the timeline for data collection for effectiveness outcomes for the parental part of the study, and duration of exposure to the Nutrition Now resource according to point of inclusion in the intervention municipality.

**Figure 4 f4:**
[figure not shown]
Overview of timeline for data collection, and exposure to the Nutrition Now resource (consisting of e-learning resources targeting different phases in a child’s 1000 first days) in the intervention municipality in the effectiveness trial. Pregnant women and parents of children between 0-2 years of age will be recruited from October 2022 until April 2023 through the MCH centre route. Participants will be exposed to age-appropriate content of the Nutrition Now resource and will be asked to respond to successive age-specific digital questionnaires depending on whether they are pregnant or the child’s age. Participants are given access to the Nutrition Now resource after completing the first questionnaire (pretest). ECEC staff will be recruited and complete the pretest questionnaire in September 2022, before getting access to the Nutrition Now-recourse. The post-test ECEC-staff questionnaire will be distributed seven months into the implementation of the intervention.

Consenting pregnant women (at any time during pregnancy), and parents of children between 0-2 years (at any time in this age interval) will first be asked to complete a short digital questionnaire to provide socio-demographic data in addition to expected due date (for pregnant women), or child’s age (for parents). Thereafter they will be asked to complete a second questionnaire tailored to the age of the child. Access to the Nutrition Now resource will be provided when the age-specific questionnaire is completed. The dose and duration of exposure to the Nutrition Now resource will differ between the participants depending on when they enter the study. Only those who are pregnant when entering the study between October 2022 and April 2023 will potentially be exposed to the whole range of intervention content, whereas a 1-year-old whose parent(s) enter the study in the same period, will be exposed to the “Toddlers 1-2 years” component and, if in ECEC, also the “Preschoolers 1+ years” component (**Figure 4**). Two-year-olds recruited at the regular health visit will be given access to the “Toddlers 1-2 years” component after completing the 24 months questionnaire.

ECEC leaders and staff will respond to questionnaires when consenting to participate in the study and seven months after getting access to the Nutrition Now resource.

Participants (both parents and ECEC staff) recruited in the control municipality will be asked to complete the same questionnaires as intervention participants but will not have access to the Nutrition Now resource.

Data on food purchase history in the ECECs will be collected from both the ECECs in the intervention and control municipality, for the years 2022 and 2023, to obtain data on fruits and vegetables purchases. Municipal budget data for 2022 and 2023 will be collected to gather info on municipal spend on activities related to early childhood nutrition and feeding practices in both the intervention and control municipality.

*Quantitative and qualitative data will be collected to evaluate the implementation process and outcomes*. Quantitative data from parents and ECEC staff at seven and 12 months after being enrolled in the study, will be collected using questionnaires with items from the seven implementation outcomes described in **Table 1**. Additional data will be collected using checklists during iterative interviews with ECEC and MCH during the first six months of the project, and usage data will be collected from the Nutrition Now resource. Evaluation of acceptability, appropriateness, and feasibility of the Nutrition Now resource will be done using a validated and generic questionnaire developed by Weiner et al. (41).

Qualitative data will be collected from short iterative interviews with team leaders in ECEC and contact persons for MCH nurses and midwifes, to promote self-reflection and continuous development. Further, focus group discussions with ECEC and MCH staff will be conducted approximately seven months after start of the implementation period to explore experiences with the implementation strategies. Individual interviews with ECEC leaders and stakeholders at municipality level will also be conducted (**Table 1**).

In depth description of what motivates and/or hinders use of the Nutrition Now resource will be explored in ethnic minority groups to render the next version of the resource more inclusive. With an anthropological way of interviewing, multi-stage, in-depth, open-ended and ethnographic interviews will be conducted with sub-samples of pregnant women and parents within ethnic minority groups in the intervention municipality to understand how the implementation of the resource works in and affects their everyday life.

*Costs related to Nutrition Now resource development, maintenance and implementation* will be collected throughout the implementation period using a bottom-up, micro-costing approach which will involve direct enumeration and costing of each intervention input (58).

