**Figure 2 f2:**
[figure not shown]
Overview of assessments, participants, and types of outcome measures in the mixed methods Hybrid 1 trial of the Nutrition Now project. **(A)** Ethnic minorities invited to participate in qualitative interviews in addition to the assessment that applies to all recruited pregnant women/parents of 0-2 year-olds. **(B)** ECEC staff champions and MCH staff contact persons are appointed staff members invited to participate in short iterative interviews. **(C)** ECEC leaders provide socio-demographic data for the effectiveness evaluation to be assessed at the ECEC level in addition to qualitative interviews.

**Table 1 T1:** Effectiveness, implementation and cost-effectiveness outcomes in Nutrition Now.

Outcomes	Evaluation data	Data collection tool	Level
Effectiveness			
Aspects of child diet quality^1^	Frequency of intake of fruits, vegetables, pulses, and sugary drinks.	Short food frequency web-based questionnaire.	Individual
Breastfeeding^2^	Intention of breastfeeding, exclusive breastfeeding duration and any breastfeeding duration	Short web-based questionnaire	Individual
Child eating enjoyment^2^	Child Eating-enjoyment, reported by parents and ECEC staff	Child eating-enjoyment scale (37)	Individual
Child quality of life^2^	Pediatric Quality of Life Infant Scales	PedsQL (38) – Web-based questionnaire	Individual
Child development^2^	Developmental milestones	Ages and stages (18 months) ASQ3 (39)	Individual
Anthropometric measures (mother, child) ^2^	Weight change in pregnancy, mother’s weight and height, child’s weight and length	Short digital web-based questionnaire	Individual
Pregnancy complications	Preeclampsia, gestational diabetes, preterm delivery		Individual
Maternal diet in pregnancy^2^	Diet quality score	Diet screener, web-based questionnaire	Individual
Maternal quality of life^2^	Satisfaction with life score	SWLS - Satisfaction with life scale (40) – Web-based questionnaire	Individual
Parental meal- and feeding practices^2^	Role modelling, responsive feeding, family meal participation, meal distractions, frequency of home cooking, repeated exposure.	Short digital web-based questionnaire	Individual
ECEC staff meal- and feeding practices^2^	Role modelling, meal practices, repeated exposure, collaboration with parents.	Short digital web-based questionnaire	Individual/organizational

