### 2.9 Analysis

#### 2.9.1 Effectiveness

Evaluating our effectiveness objective requires following a treatment policy estimand strategy (59, 60)- that is the effect of access to the Nutrition Now resource regardless of post-enrolment or intercurrent events such as non-compliance or discontinuation. This necessitates that outcome data be collected regardless of level of engagement and assumes that missing data are missing not at random (MNAR). Statistical models appropriate for de facto estimands will thus be used and the effect of MNAR on our effectiveness estimates will be assessed using sensitivity analyses. Confounding due to the non-randomised nature of the study, e.g., household size and income, parental education, ECEC status (public or private), will be assessed and adjusted for using regression models.

The main comparison will be between children and parents given access to all Nutrition Now components and those in the control municipality. Similar estimators of the Nutrition Now effectiveness will be available from comparisons within the intervention municipality since we will have data on approximately 100 parent-offspring pairs completely unexposed to the Nutrition Now resource as a result of the recruitment design (described above). The latter comparisons will improve causal inference by triangulating the evidence from two designs with different sources of bias (61). In this example they act as a sensitivity analysis to assess bias from residual confounding.

The recruitment strategy also creates variation in the number of components of the Nutrition Now resource each observational unit will be exposed to. Combined with the serial data collection points (pregnancy, 6 weeks, 6, 12, 18 and 24 months), we will be able to assess the effectiveness of each component of the resource in addition to duration of access.

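### No measurement of maternal diet in pregnancy or breastfeeding intention is described after access is given, so on the stated schedule these two secondary outcomes compare baselines

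*Protocol article*

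**What the plan says.** **Outcomes.** Table 1 of the protocol article marks "Maternal diet in pregnancy" as a secondary effectiveness outcome, scored from a web-based diet screener. The breastfeeding outcome, also secondary, consists of "Intention of breastfeeding, exclusive breastfeeding duration and any breastfeeding duration". Section 2.2.1 lists maternal diet and breastfeeding again among the secondary outcomes.

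**Schedule.** Section 2.8 has pregnant women and parents "assessed during pregnancy, at child ages 6 weeks, 6 months, 12 months, 18 months, 24 months". Section 2.9.1 repeats this as "serial data collection points (pregnancy, 6 weeks, 6, 12, 18 and 24 months".

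**Entry and access.** Section 2.8 enrols "Consenting pregnant women (at any time during pregnancy" as well as parents of children up to 2 years. Each participant first gives socio-demographic data and then completes a questionnaire matched to her stage; access opens once this second questionnaire is done. The Figure 4 legend agrees: "Participants are given access to the Nutrition Now resource after completing the first questionnaire (pretest". Section 2.3 also places the pretest before access. Control participants answer the same questionnaires and get no access.

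**Estimand.** Section 2.9.1 defines the target as the effect of having access, under a treatment policy strategy.

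**The concern.** Diet during pregnancy is a target of the interventions merged into the resource (Introduction), and section 2.9.1 undertakes to assess the effectiveness of each component. Maternal diet in pregnancy is the most direct outcome of the pregnancy content.

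If its only measurement comes before access, the between-municipality result cannot inform that question in either direction. A difference between two non-equivalent municipalities could be reported as an effect of the resource. The absence of a difference could be reported as failure of the pregnancy component. The same applies to breastfeeding intention.

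**Working it through.** No stated figure is in dispute. The check is mainly one of order.

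**1. The path of a woman enrolled in pregnancy, intervention municipality**

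| Step | Event | Source | Access yet? |
|---|---|---|---|
| 1 | Socio-demographic form and due date | 2.8 | No |
| 2 | Pregnancy questionnaire (her stage-specific one) | 2.8 | No |
| 3 | Access opens | 2.8, Figure 4 legend, 2.3 | From here |
| 4 | Next questionnaire named: child age 6 weeks | 2.8, 2.9.1 | Yes |

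The pretest cannot be read as the socio-demographic form alone, because section 2.8 makes access depend on the stage-specific questionnaire. Between steps 3 and 4 the text names no assessment. A woman who enrols after birth starts with a postnatal questionnaire.

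**2. The protocol applies the same logic elsewhere.** Two-year-olds recruited at the routine visit get access after the 24-month questionnaire, and section 2.9.1 counts approximately 100 parent-child pairs as completely unexposed because of how recruitment works. An entry questionnaire that yields unexposed data at 24 months yields unexposed data in pregnancy too.

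**3. What the comparison would estimate.** For a score taken before access:

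expected difference (intervention − control) = baseline difference between municipalities + effect of municipality-level activity before access + 0 × effect of access.

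The second term is possible because Tables 3 and 4 describe newspaper coverage and staff education before implementation. Neither of the first two terms is the stated estimand. Covariate adjustment may shrink the first term but cannot change the zero. The comparison within the intervention municipality does not help, since no post-access pregnancy value is described there either.

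**4. Illustration of size.** The documents give no standard deviation for the diet score, so the scale is borrowed from the vegetable-intake power statement in section 2.5 (0.5 items per day, alpha 0.05, 80% power, 100 exposed). Assuming a two-sided test with 100 per group:

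SD = 0.5 / [(1.960 + 0.842) × √(2/100)] = 0.5 / 0.396 = 1.26 items per day.

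Simulated rejection rates (10,000 runs, two-sided t-test, 100 per group, no baseline difference):

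| True effect of access | In SD units | Measured before access | Measured after access |
|---|---|---|---|
| 0 | 0 | 5.5% | 5.5% |
| 0.5 | 0.5/1.26 = 0.40 | 5.2% | 79% |
| 1.0 | 1.0/1.26 = 0.79 | 4.9% | 100% |

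The pre-access column stays near 5% whatever the resource does. The t-test cannot tell a baseline shift from an effect. A pre-existing difference of 0.40 SD between the municipalities would therefore be declared significant in the same 79% of studies, with no effect of access at all. The figures illustrate the mechanism; the conclusion rests on steps 1 to 3.

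**The case against.** The best reply is that the text never says the pregnancy questionnaire is given once. An assessment during pregnancy is an open interval, and the list in section 2.9.1 may be shorthand. Section 2.8 refers to Figure 4 for the timeline, and the figure is not reproduced in the text at hand. Table 1 does not tie the diet screener to a wave. Some pregnancy information, such as preterm delivery, has to be gathered at or after birth, so a diet recall item at 6 weeks is conceivable. An article may also leave the content of each questionnaire to the full protocol.

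Part of this stands. It would be too strong to say that these outcomes can never show an effect or that every measurement certainly precedes access: a second wave or a recall item is not excluded. What does not stand is that this is only omitted detail. The schedule is stated twice with one pregnancy point, the access rule is explicit, and following both as written leaves nothing after access.

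Two further inferences are not supported:

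- **That power is 5%.** This holds only if the municipalities do not differ at baseline. They are not randomised, and sections 2.9.1 and 3 acknowledge confounding and selection bias.
- **That not asking postnatal entrants about pregnancy is a gap.** They had no access in pregnancy, so they could show no effect of access on it.

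**Conclusion.** The point holds in a limited form. On the stated schedule and access rule, the pregnancy questionnaire described for a woman enrolled in pregnancy is her pretest, and no post-access measurement of maternal diet in pregnancy or breastfeeding intention is described. A comparison of the municipalities on these measures would be a comparison of baselines and could not estimate the effect of access.

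This rests on one assumption: that Figure 4 and the questionnaires contain no later pregnancy wave or recall item. If they do, stating it settles the matter.

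The scope is one secondary outcome and one of three parts of another. Section 2.5 expects 100–160 participants per municipality to be potentially exposed from pregnancy onwards; these are the women whose pregnancy values would all be pre-access. Exclusive and any breastfeeding duration, pregnancy weight change and pregnancy complications can be ascertained after access, and the primary outcome is untouched. The issue should be corrected, but it does not threaten the main comparison.

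**What to change.** First check Figure 4 and the questionnaires. If a post-access measurement exists, name its timing in section 2.8 and Table 1.

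If not, choose one of the following, identically in both municipalities:

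1. **Late-pregnancy web questionnaire after access**, timed from the due date already collected, repeating the short diet screener and, for women still pregnant, the breastfeeding intention item.
2. **Diet screener in the 6-week questionnaire**, referring to late pregnancy. This covers diet only; intention would still need option 1 or 3.
3. **Reclassification** of the two measures as baseline covariates, with no claim of effectiveness on them.

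Under options 1 and 2, analyse the post-access score adjusted for the pre-access score and gestational week at entry, since entry is allowed at any stage of pregnancy.

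The cost is a few items in the existing web system and a short amendment. The drawbacks are slight extra burden, few post-access weeks for women who enter late in pregnancy, and recall error under option 2. Option 3 needs only a change of text, but leaves the direct effect on pregnancy diet unassessed.

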We have previously developed and reported on the efficacy of four interventions that target diet during pregnancy, parental feeding practices, and ECEC diet quality and meal environment, respectively. All four interventions have shown promising indications of dietary improvement (28–32) (**Additional File 1, Table S1**). These interventions are digital, largely video-based and grounded in social cognitive theory (33), addressing the interaction between person, environment, and behaviour. In the Nutrition Now project, we have combined these four interventions into one joint e-learning resource (the Nutrition Now resource) for parents, MCH staff and ECEC staff. The Nutrition Now resource will be implemented in one municipality through municipal services for MCH care (age: 0-2 years) and ECEC departments for children aged 1-3 years, as shown in **Figure 1**, which depicts hypothesised mechanisms to explain how the intervention may work. Increased knowledge, skills, and motivation are thought to improve dietary behaviors and feeding practices that will in turn affect pregnancy, infant and toddler health outcomes. We also aim for the implementation to influence local policy relating to physical and social aspects of the food environment. The ultimate goal of the Nutrition Now project is to reduce the burden of obesity and NCDs and improve health in quality of life in Norway through improved diet and diet-related behavior in the first 1000 days of life (**Figure 1**).

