ECEC fruit and vegetable availability^2^	Fruit and vegetables purchases in ECEC	Receipts collected retrospectively, digital when available.	Organizational level
Municipal spend on nutrition ^2^	Resources (staff/money) allocated to nutrition or food-related activities over the annual budget in the municipality.	Publicly available political protocol documents. Collected retrospectively.	Community level
Implementation			
Acceptability	Whether Nutrition Now is liked, welcomed, appealing and approved	AIM-scale (41) Web-based questionnaire Interviews	Individual (a,b,d), and organizational (e,f,g)
Appropriateness	Whether Nutrition Now is fitting, suitable, applicable and a good match	IAM-scale (41) Web-based questionnaire Interviews	Individual (a,b,d), and organizational (e,f,g)
Feasibility	Whether Nutrition Now is implementable, possible, doable and easy to use	FIM-scale (41) Web-based questionnaire Interviews	Individual (a,b,d) and organizational (e,f,g)
Reach	Number of users (incl. ECEC) and characteristics of users	Data from website	Individual and organizational
Adoption/Uptake	Number of participants (incl ECEC)/number invited, what parts of the resources are used, and for how long.	Data from recruitment Interviews	Individual (a,b) and organizational (e,f,g)
Implementation/Fidelity	To what extent Nutrition Now is delivered as planned	RE-AIM.org (42) Interviews	Individual (a,b) and organizational (e,f,g)
Maintenance/Sustainability	To what extent Nutrition Now is still being used 7 and 12 months after implementation, how it is adapted.	RE-AIM.org (43) Interviews	Individual (a,b), organizational (e,f,g), community.
Cost-effectiveness			
Implementation costs	Costs of implementing the e-resource, including monitoring activities and management. Costs of the time spent by MCH and ECEC staff in using the resource.	Implementation costs/effectiveness outcomes	Organizational
Nutrition Now effectiveness outcomes	Quality of life score and developmental milestones.	PedsQL, Ages and stages (18 months) ASQ3 (39) in short digital questionnaire	Individual

^1^ Primary effectiveness outcome, ^2^ Secondary effectiveness outcome. Implementation outcomes will also be assessed in qualitative interviews. Level: Individual: ECEC staff (a), Health care center staff (nurses and midwifes) (b), pregnant women (c), parents of 0-24 months old children (d).

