#### 2.2.1 Effectiveness outcomes

The primary effectiveness outcome is aspects of child diet quality, represented by intake of vegetables, fruits and berries, legumes/pulses and sugar sweetened beverages. Secondary outcomes include a) breastfeeding rates (including mixed feeding), b) child eating enjoyment c) health-related quality of life (infant), d) child development measures, e) self-reported anthropometrics (parental and child), f) maternal diet, g) maternal quality-of-life measures h) pregnancy complications, i) parental feeding practices, j) ECEC staff feeding practices k) ECEC fruit and vegetable availability and l) municipal spend on activities related to early childhood nutrition and feeding practices (see **Table 1**).

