### 2.3 Study design

In this hybrid type 1 mixed methods implementation study we use a quasi-experimental design. The CONSORT Extension for pragmatic trials with its checklist was used (47). A single intervention municipality will be given access to the Nutrition Now resource and another control municipality (non-equivalent control) will continue as normal (**Figure 2**). Data from participants resident in the intervention municipality will be collected in the form of a pretest before they are given access to the Nutrition Now resource. Subsequently post-test data will be collected until the child reaches 2 years of age (See Data collection). Participants in the control municipality will be asked to provide pre- and post-test data but will not receive access to the Nutrition Now resource. Additionally, a time-series design will be used for comparisons within the intervention municipality between groups of participants exposed to the Nutrition Now resource at different levels of duration, and different types of exposure (See Data collection).

Enrolment started September 2022. The anticipated recruitment period is from September 2022-to April 2023, and we envision that the last participant (if recruited in early pregnancy in April 2023) will complete the study in September 2025. The ECECs were recruited prior to September 2022 and MCH personnel and parents will be recruited autumn 2022.

Intervention municipality provision of access to the Nutrition Now resource starts upon enrollment in the study and is expected to continue beyond the study period as long as the municipality finds it useful.

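### Municipal spend is collected for 2022 and 2023 only, so at most one budget per municipality follows first access and the later budgets within the study are left out

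*Protocol article*

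**What the plan says.** Section 2.2.1 of the protocol article lists as its last secondary effectiveness outcome, item l, "municipal spend on activities related to early childhood nutrition and feeding practices". Table 1 places it at community level and defines the evaluation data as "Resources (staff/money) allocated to nutrition or food-related activities over the annual budget in the municipality". The source is given as "Publicly available political protocol documents. Collected retrospectively".

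Section 2.8 sets the window, for both municipalities: "Municipal budget data for 2022 and 2023 will be collected to gather info on municipal spend". No reason is given for stopping at 2023.

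The timing of the intervention is as follows. Section 2.3 says "Enrolment started September 2022" and "The anticipated recruitment period is from September 2022-to April 2023", with the last participant finishing in September 2025. The Figure 4 legend says "ECEC staff will be recruited and complete the pretest questionnaire in September 2022, before getting access to the Nutrition Now-recourse", and has parents entering through the maternal and child health centre from October 2022 to April 2023.

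The outcome serves a stated purpose. The Introduction says: "We also aim for the implementation to influence local policy relating to physical and social aspects of the food environment".

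**The concern.** An annual budget records a decision usually taken before the year it covers. If the adopted budget is what is read, the 2023 figure was settled when the resource had only just become available, while families were still being recruited and before any of the 7-month or 12-month results existed. The first budgets that could respond to experience with the resource are those for 2024 and 2025. Both are set while the study is running, and neither is collected.

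A null result on this outcome would then say little about whether the resource changes municipal priorities, because the budget may already have been decided. A difference would be hard to read as well. With one year on each side there is no earlier year to show the prior trend and no later year to show whether a change lasted.

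**Working it through.** The protocol gives no sample size, power or effect size for this outcome, so there is no stated figure to reproduce. The check is calendar arithmetic.

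**Inputs from the protocol article**
- Budget years collected: 2022 and 2023 (section 2.8).
- First access: between 1 September and 31 October 2022, as the widest reading of section 2.3 and the Figure 4 legend.
- Recruitment closes: April 2023 (section 2.3).
- Study ends: September 2025 (section 2.3).

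**Input assumed**
- Adoption of each annual budget between the end of October and the end of December of the preceding year. The protocol gives no adoption date for either municipality.

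**Number of values.** 2 municipalities × 2 years = 4 numbers.

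**Gap between first access and adoption of the 2023 budget** (adoption date minus access date, in months)

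| First access | Adopted 31 Oct 2022 | Adopted 30 Nov 2022 | Adopted 31 Dec 2022 |
|---|---|---|---|
| 1 Sept 2022 | 2.0 | 3.0 | 4.0 |
| 1 Oct 2022 | 1.0 | 2.0 | 3.0 |
| 31 Oct 2022 | 0.0 | 1.0 | 2.0 |

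The range is 0 to 4 months. Adoption on 31 December 2022 also falls 3.9 months before recruitment closes on 30 April 2023.

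**Later budgets under the same assumption.** Each further year adds 12 months. The 2024 budget is set 0 + 12 = 12 to 4 + 12 = 16 months after first access, and the 2025 budget 24 to 28 months after. With access on 1 October 2022 and year-end adoption, the three gaps are about 3, 15 and 27 months. Adding both years raises the number of budgets decided after first access from one to three per municipality.

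**If in-year revisions or accounts are read instead.** All 12 months of 2023 follow first access. From 1 October 2022 to 31 December 2023 is 15.0 months, and to 30 September 2025 is 36.0 months: 15/36 = 42%. Counted from 1 September 2022 it is 16/37 = 43%.

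**The baseline year on that reading.** From 1 October or 1 September to 31 December 2022 is 25% to 33% of the year, so 2022 accounts would not be a wholly pre-access value. Under the adopted-budget reading this does not arise, because the 2022 budget was set before access began.

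**The case against.** The adoption date is not in the protocol, and the measure is called spend in section 2.2.1, section 2.8 and the row title of Table 1. The Table 1 wording does not rule out in-year revisions. A reader might infer that the outcome has almost no post-implementation measurement, or none. The documents do not support that: calendar 2023 lies wholly after first access, and even an adopted 2023 budget was probably decided at or after first access. This objection stands, and the 0 to 4 month figure is conditional for that reason.

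A reader might also infer that a 2023 shift caused by meetings with municipal leaders would be spurious. That does not follow. Table 3 lists consensus discussions with stakeholders and politicians, a formal agreement and a declaration of priority as implementation strategies, several of them before implementation. They belong to the package being delivered, and a community-level outcome may respond to them rather than to parents' use of the website. What remains is that section 2.9.1 defines the effect of interest as that of access to the resource, and a single early budget cannot separate the two.

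Third, the 36-month study length is set by the follow-up of children recruited in pregnancy. Other organisational measures use short windows: staff questionnaires at 7 months, implementation outcomes at 7 and 12 months, and food purchases for the same two years. So 36 months is not the only fair yardstick. But a staff questionnaire can respond within 7 months, whereas an annual budget can respond only at its next adoption, so a short window costs this outcome more.

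Last, this is one of twelve secondary outcomes, the primary outcome is untouched, and extra years cannot remove the limit of one municipality per arm. That stands, and it keeps the point minor.

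**Conclusion.** The point holds as a minor design weakness. The year window is a stated choice, not a detail left to a fuller document, and it gives one earlier and one later value per municipality. If the 2023 budget was adopted between the end of October and the end of December 2022, it was decided about 0 to 4 months after first access and before recruitment closed. It could reflect the earlier municipal engagement, but hardly any response to experience with the resource. If revisions or accounts are read, up to 12 post-access months of 2023 are covered, but observation still stops at about 15 of 36 months. On either reading, the years in which a policy response would be most likely to show are not collected.

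The conclusion rests on one assumption from outside the protocol, the adoption date. It also depends on which documents are read, which the article does not settle.

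**What to change.** In section 2.8, extend municipal budget collection in both municipalities to 2024 and 2025, and add 2021 as a further pre-access year, using the same public documents. Interpret 2023 as an early or transition year. State whether adopted budgets, revisions or accounts are read, and use the same type in every year and in both municipalities. Adopted budgets fit the timeline best: under the assumption above, the 2025 budget is available before the study ends in September 2025, whereas full-year 2025 accounts would not be.

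The cost is a few hours of extra document extraction, with no participant burden and no change to the timeline. With one municipality per arm, the comparison should still be reported as descriptive.
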